## Abstract

**Background and Aims:**

Moral courage is vital in nursing, enabling professionals to make ethical decisions and uphold values, even in challenging situations. Nursing students often struggle with moral decision‐making due to limited experience and insufficient ethical training. This study proposes a randomized controlled trial (RCT) to evaluate the effectiveness of scenario‐based ethics training compared to traditional methods in improving professional moral courage among nursing students.

**Methods and Analysis:**

This RCT involved a 3‐month scenario‐based ethics training program delivered under faculty supervision, targeting sixth‐semester undergraduate nursing students. Participants (*n* = 48) were randomly assigned to either the intervention group or the control group. Both groups received traditional ethics education, however, the intervention group also participated in two workshops focused on core and derived ethical concepts (e.g., autonomy, confidentiality) utilizing a scenario‐based approach. This was followed by weekly online follow‐ups and discussions conducted via WhatsApp Messenger. The outcomes will be assessed using the Sekerka Professional Moral Courage Questionnaire at four time points: immediately before, immediately after, and at 1 and 3 months postintervention. The questionnaire has demonstrated acceptable validity and reliability in previous studies, with Cronbach's *α* exceeding 0.8, and a value of 0.977 reported in an Iranian validation study. In this study, face validity was confirmed by ten nursing faculty members. The data will be analyzed using *t*‐tests, *χ*
^2^ tests, and ANCOVA to evaluate changes in professional moral courage (SPSS v22, *p* < 0.05).

**Conclusion:**

This protocol outlines a trial to evaluate the impact of scenario‐based training on enhancing nursing students' professional moral courage and improving ethics education in clinical settings.

**Trial Registration:**

Iranian Clinical Trials Registry: IRCT20240319061338N1.

## Introduction

1

Ethics is an essential and inseparable part of human life, addressing behaviors, ideal ways of living, and distinguishing between good and evil [1]. With the increasing complexity of life, ethical challenges have also become more prevalent, leading to negative consequences for mental health [2]. Nurses, especially in care settings, frequently face ethical dilemmas, and factors such as staff shortages, organizational misalignment, and managerial weaknesses exacerbate these challenges [3, 4]. These issues can lead to burnout and even result in nurses leaving the profession [5].

Nursing students also require skills in ethical analysis and decision‐making to cope with the expectations and complexities of clinical settings [6, 7]. However, many of them find dealing with moral distress difficult due to fear of taking ethically appropriate actions [8]. To overcome these challenges, they need moral courage, which entails commitment to principles and the willingness to accept risks in ethical decision‐making [9, 10].

Moral courage is a fundamental concept in the nursing profession, helping nurses provide valuable and professional care to patients and society while embodying desirable human qualities [11]. Moral courage entails making decisions and taking actions based on ethical values, even in challenging situations. This virtue is essential for healthcare professionals to overcome ethical conflicts and professional challenges with a clear conscience [12]. It bridges the gap between awareness of professional values and commitments and their implementation, even in the face of risks such as social rejection and shame, allowing individuals to accept vulnerability to uphold their values [13].

According to Sekerka and colleagues, moral courage is adherence to ethical principles when faced with challenges and confronting moral corruption, particularly in making difficult decisions under challenging circumstances [14]. It is considered a multidimensional construct, involving ethical sensitivity, emotional resilience, and the behavioral readiness to act upon one's values despite potential risks. Rather than being a fixed personality trait, moral courage encompasses a set of professional attitudes and competencies that can be nurtured and strengthened through experience and targeted ethical education [14]. Nurses must be familiar with ethical issues to perform professionally, and this sensitivity should be emphasized during their education [15]. Although ethical training is included in the nursing curriculum, mainly through the “Professional Ethics and Communication Skills” course delivered via lectures, this traditional training is often insufficient to prepare students for the ethical challenges of clinical practice [6]. A lack of clinical experience, low self‐confidence, and inadequate education diminish students' capacity for moral courage and gradually reduce their ethical sensitivity [16, 17].

Nursing students need specific skills to effectively cope with moral distress, and nursing educators are responsible for providing learning experiences that prepare them to face ethical issues [6]. Teaching ethics to students fosters a deeper understanding of perspectives and their effective participation in addressing ethical challenges after graduation. For this reason, ethical principles are considered a cornerstone of the nursing curriculum [18]. Some studies suggest that teaching moral concepts enhances moral sensitivity; however, traditional teaching methods, such as lecture‐based and rule‐oriented instruction, primarily focus on the transmission of theoretical content and professional codes, with limited emphasis on critical thinking or real‐life application. As a result, they may fail to adequately prepare students for ethical decision‐making in complex clinical environments [19, 20, 21].

Scenario‐based training, as an interactive approach, enhances students' decision‐making skills and prepares them to face ethical challenges in difficult situations [21, 22]. While previous research has focused on issues like moral distress and moral courage among nurses, few studies have examined these issues among nursing students. Understanding the factors that influence students' moral courage can help healthcare and educational stakeholders design appropriate interventions to enhance moral courage among students [22, 23].

Innovative teaching methods, such as scenario‐based training, which remains limited in Iran, may potentially improve students' ethical skills and abilities. This approach can guide students toward a deeper understanding of ethical concepts, strengthen professional behaviors, and foster an ethical culture in educational and professional settings [21]. By presenting realistic scenarios, it is possible to enhance students' moral resilience against the pressures and challenges of the healthcare system [24].

Based on the literature review, moral courage is essential for professional decision‐making in the nursing profession; however, traditional teaching methods fail to prepare students to address ethical challenges adequately. Scenario‐based training may have the potential to enhance students' ethical competencies. Despite the importance of this issue, to the best of our knowledge, no study has yet examined the impact of scenario‐based training on nursing students' professional moral courage. This study aims to fill this gap by investigating how scenario‐based training of moral concepts compares with traditional teaching methods. Accordingly, this study aims to investigate the impact of scenario‐based moral concepts training on the professional moral courage of nursing students, with the hypothesis that scenario‐based ethics training will significantly increase the professional moral courage of nursing students compared to traditional teaching methods.

## Methods/Design

2

### Study Design

2.1

The present study is a randomized controlled trial (RCT) conducted at a single site and in an open‐label format. The study involves two groups: a control group and an intervention group, aiming to investigate the impact of scenario‐based training on moral concepts on the professional moral courage of nursing students. This protocol has been developed in accordance with the 2022 Standard Protocol Items: Recommendations for Interventional Trials (SPIRIT) guidelines [25].

### Study Setting

2.2

The study will be conducted at the School of Nursing and Midwifery, Tehran University of Medical Sciences. As one of the primary nursing education centers in Iran, this school provides an appropriate environment for implementing the research.

### Eligibility Criteria

2.3

The nursing students enrolled in the School of Nursing and Midwifery will be assessed based on the following eligibility criteria.

#### Inclusion Criteria

2.3.1

Participants will be included in the study if they meet the following conditions: (1) willingness to participate in the study, (2) successful completion of the theoretical course on professional ethics, (3) at least 1 year of clinical experience as a nursing student (internship or externship), and (4) access to and ability to use a smartphone and the internet.

#### Exclusion Criteria

2.3.2

Participants will be excluded or withdrawn from the study if they: (1) have been diagnosed with psychological or cognitive disorders, (2) have previously participated in similar ethical empowerment workshops, and (3) fail to attend one of the scheduled ethics workshops in the program.

Information regarding psychological or cognitive disorders will be obtained solely through voluntary self‐reporting by participants during the eligibility screening process. No medical records will be accessed, and responses will be kept strictly confidential by the researcher in accordance with ethical approval protocols.

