#### Scenario‐Based Moral Concepts Workshop for the Intervention Group

2.4.1

A moral concepts workshop will be held for the intervention group. At the beginning of the first workshop, after obtaining students' phone numbers, a collaborative group will be created on an internet‐based social media platform (WhatsApp). This group will include the researcher and the nursing ethics professor from the School of Nursing, Tehran University of Medical Sciences, to enhance the training, provide long‐term follow‐ups, and monitor the students in various aspects. The intervention group will receive the educational program on moral concepts through two 2‐h workshops over 2 consecutive days. In the first workshop, the basic principles of medical ethics will be discussed, and in the second, concepts derived from these principles will be analyzed.

The pedagogical approach used in this training intervention was based on constructivist and experiential learning models. This approach emphasizes active participation, collaborative problem‐solving, and reflective thinking. Through scenario‐based learning, students are exposed to complex ethical dilemmas similar to those encountered in real clinical settings, allowing them to apply theoretical knowledge in a practical, decision‐oriented environment. The intervention was designed to encourage critical thinking, moral reasoning, and confidence in ethical decision‐making.

The curriculum of the training was structured around the four core principles of biomedical ethics—autonomy, beneficence, nonmaleficence, and justice—as well as key derived ethical concepts such as confidentiality, honesty, disclosure, and moral courage. These concepts were selected based on the foundational biomedical ethics framework proposed by Beauchamp and Childress, and the professional codes of ethics developed by the American Nurses Association (ANA) and the International Council of Nurses (ICN). Their contextual relevance and educational priority were confirmed through expert review by ten faculty members specializing in nursing ethics at Tehran University of Medical Sciences.

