#### Traditional Training

2.4.3

The students in the control group will not receive the scenario‐based intervention program designed for the intervention group. However, they will receive the traditional training in ethics routinely offered at the university, which consists of the “Professional Ethics and Communication Skills” course. This course is part of the standard nursing curriculum, typically delivered during the second semester, and is presented through lectures. It covers essential topics such as ethical principles (e.g., beneficence, nonmaleficence, autonomy, justice), communication strategies, and professional behavior. The content is primarily theoretical, instructor‐centered, and does not include interactive or scenario‐based activities. Meanwhile, the students in the intervention group will receive, in addition to this traditional training, a scenario‐based ethics training program. Furthermore, all educational materials related to the intervention will be provided to the control group after the study is completed and after the primary outcome variable has been measured.

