### Data Collection

2.6

In this study, data will be collected using two questionnaires: a demographic information questionnaire and the Professional Moral Courage questionnaire by Sekerka et al. [14]. The demographic information of the students will be gathered through a written questionnaire at the beginning of the study. Data on the dependent variable (Professional Moral Courage) will be collected immediately before the workshop, immediately after the workshop, 1 month later, and 3 months after the intervention. Both the intervention and control groups will be assessed for this variable, and they will complete the standardized Professional Moral Courage questionnaire by Sekerka et al. [14] in person using printed paper and pencil.

To prevent information leakage and sample contamination, the control group will complete the study first, followed by the intervention group.

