### Recruitment

2.8

To conduct this study, the researcher will first obtain permission from the Joint Ethical Committee of the School of Nursing and Midwifery and the School of Rehabilitation at Tehran University of Medical Sciences, as well as permission from the Dean of the School of Nursing and Midwifery. The researcher will then visit the School of Nursing and Midwifery to select samples based on the inclusion criteria. All undergraduate nursing students from 6th semester, which includes two classes, will be considered for the study. Eligible participants will be selected through a census. A list of students will be obtained from the school administration, and students will be invited to participate by the principal investigator during an in‐person meeting. After explaining the study's aims and methods, informed consent will be obtained from all participants. The classes will be randomly assigned to either the intervention group (Class A) or the control group (Class B) using simple randomization. In this phase, further explanations about the study will be provided, and students will be encouraged to follow the study's timeline. To minimize the risk of contamination between the classes and prevent information leakage between the two groups, the control group will be included in the study first, followed by the intervention group.

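### Exclusion criterion (3) withdraws students who miss a workshop; it acts after allocation and only in the intervention class, so one arm alone is filtered on attendance

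*Protocol article*

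**What the plan says.** Section 2.3.2 (Exclusion Criteria) opens with "Participants will be excluded or withdrawn from the study if they" and gives as its third item that they "fail to attend one of the scheduled ethics workshops in the program". The consequence named is removal from the study, not only from the training.

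The workshops belong to one arm. Section 2.4.1 says "A moral concepts workshop will be held for the intervention group", delivered "through two 2‐h workshops over 2 consecutive days". Section 2.4.3 says "The students in the control group will not receive the scenario‐based intervention program designed for the intervention group". The ethics teaching that both arms share is a second-semester lecture course, and section 2.3.1 already requires "successful completion of the theoretical course on professional ethics" of everyone at entry.

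On timing, section 2.8 describes consent and then allocation: "The classes will be randomly assigned to either the intervention group (Class A) or the control group (Class B) using simple randomization". The workshops come afterwards. Section 2.6 adds that "the control group will complete the study first, followed by the intervention group".

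Section 2.12 (Statistical Analysis) names paired t-tests within groups and ANCOVA for confounders. It does not list the ANCOVA covariates. Nothing in the article says that students withdrawn under criterion (3) go on to complete the later questionnaires or are analysed as allocated.

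**The concern.** An eligibility criterion is something that can be known at screening. Workshop attendance cannot: it is a response to the allocated programme, observed after the coin flip. Listing it as an exclusion criterion turns non-adherence in one arm into removal from the trial.

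The hypothesis in the Introduction is a between-group one, scenario-based training against traditional teaching. Under the rule, an intervention student who skips one 2-hour session drops out of that comparison, while a control student who would have skipped it stays in. The outcome is a self-completed questionnaire in an open-label study, and willingness to turn up plausibly goes with engagement in the subject. At stake is part of any observed difference being due to who was kept and not to what they were taught.

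**Working it through.** **Can a control student meet criterion (3)?** The criterion needs a scheduled workshop to miss. Section 2.4.1 schedules workshops for the intervention group, and section 2.4.3 gives the control group none. The control group's lecture course was completed before entry. So the answer is no, and the filter is one-sided by construction.

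**Does it act after allocation?** The order is consent, allocation of classes (sections 2.8 and 2.9), then workshops (section 2.4). So the answer is yes.

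**The plan's own sample size.** Inputs from section 2.7: effect size 1.18, alpha 0.05 (the formula uses alpha/2, so two-sided), power 0.95. For a two-sample t-test the noncentrality is d × sqrt(n1·n2/(n1+n2)). With 20 per arm this is 1.18 × sqrt(10) = 3.73, giving power 0.953. So 40 in total is reproduced, and 40 × 1.2 = 48 matches the stated total.

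**Does the rule threaten power?** Take 48/2 = 24 per class (an assumption, as class sizes are not given) and treat students as independent.

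| Analysed, intervention v control | Power at d = 1.18 |
|---|---|
| 24 v 24 | 0.979 |
| 19 v 24 (about 20% of the intervention class removed) | 0.963 |
| 16 v 24 (all 48 − 40 = 8 spare students lost from one class) | 0.945 |

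The figures stay at or close to the planned 0.95. Power is not the harm.

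**How large could the selection bias be?** None of these inputs is in the documents. Assume no true effect, a fraction p of the intervention class removed (those with the lowest propensity to attend), and a correlation r between that propensity and the outcome score. For an unadjusted comparison of post-workshop scores:

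bias (in SD) = r × φ(z_p)/(1 − p)

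- p = 0.10: φ(z_p)/(1 − p) = 0.1755/0.90 = 0.195
- p = 0.20: φ(z_p)/(1 − p) = 0.2800/0.80 = 0.350

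| p | r = 0 | r = 0.3 | r = 0.5 |
|---|---|---|---|
| 0.10 | 0 | 0.058 | 0.097 |
| 0.20 | 0 | 0.105 | 0.175 |

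A simulation of 40,000 trials with 24 students per class agrees. With 19 of 24 intervention students kept, the bias was 0.104 SD (r = 0.3) and 0.173 SD (r = 0.5). The type I error was 0.065 and 0.091 against a nominal 0.05. With 22 of 24 kept, which is slightly under 10% removed, the bias was 0.047 and 0.078 SD. Over roughly 10-30% removed and r = 0.2-0.5, bias ran from 0.03 to 0.23 SD and type I error from 0.052 to 0.118. At r = 0 there was no bias and type I error was 0.05.

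**What would baseline adjustment do?** Suppose propensity to attend correlates equally with baseline and later scores, and the pre-post correlation is 0.7 (also an assumption). ANCOVA on baseline then leaves about (1 − 0.7) of the bias: 0.105 × 0.3 ≈ 0.03 SD.

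**The case against.** Several points against the concern have force.

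- **The size rests on assumptions.** The documents give no expected non-attendance, no correlation and no class sizes, and the exposure is only two short sessions on consecutive days. The figures are also small beside a planned effect of 1.18. This stands: they show what the rule could do and do not estimate what it will do.
- **Adjustment may shrink the bias.** Every student is due a pre-workshop score. If ANCOVA includes it, selection on a stable trait is largely removed, as shown above. This stands too, although section 2.12 does not say that baseline is a covariate. Adjustment also cannot remove selection on unmeasured engagement or on response to the training.
- **The analysis population may be in a separate plan.** That is true, and its absence from an article is no fault. But the rule is stated here, and it removes students from the study. An analysis plan cannot supply outcomes that were never collected.
- **The control class is selected as well.** Its students must consent and return for four paper questionnaires, and less engaged ones can be lost. This stands: the control class is free of selection on attendance only.

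A reader might go further than the text allows in three ways. One is to infer that questionnaires definitely stop at withdrawal, so that an as-allocated analysis is impossible. That is the ordinary meaning of withdrawal from a study, but the article does not say it. Another is to infer that the estimate is certainly biased towards the training. The direction is an inference about motivation, and no section says why students would miss a session. The third is to infer that the attrition allowance is exhausted and power lost, which the arithmetic does not support.

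**Conclusion.** The concern holds as a fault in a stated rule. Criterion (3) acts after allocation, can be met only in the intervention class, and leaves that class filtered on attendance while the control class is not. Nothing else in the article repairs this.

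The probable direction is in favour of the training, provided that attendance is related to motivation and so to moral courage. The illustrative size is about 0.06-0.18 SD, for 10-20% removed, a correlation of 0.3-0.5 and no baseline adjustment. It would be smaller with baseline-adjusted ANCOVA and nil without correlation. The practical urgency comes from the likelihood that withdrawn students are not measured again, which later analysis may be unable to undo.

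Allocating one whole class per arm is a separate and serious problem. This point neither depends on it nor resolves it.

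**What to change.** - Delete criterion (3) as a reason for exclusion or withdrawal, and record workshop attendance as adherence.
- Seek all four questionnaires from every allocated student, whatever their attendance.
- Analyse students in the class to which they were allocated, adjusting for the baseline score.
- Report an analysis of students who attended both workshops only as a secondary result.

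The Abstract and Table 1 describe some of the work in the past tense, so the workshops may already have run. If they have, and outcomes were not collected from withdrawn students, report how many were withdrawn under this rule and add a sensitivity analysis for their missing scores.

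The cost is an amendment to an approved and registered protocol, a few more paper questionnaires, and a slight dilution of the effect by non-attenders.
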